### Data management and statistical analysis

The first and second author have the daily responsibility for overseeing patient safety, study design, database integrity and study conduct and have access to the final study dataset. No data will be entered before the intervention is finalised, to make sure that the baseline data will not influence the intervention. A random check of at least 20% of entered data will be performed to ensure data quality before starting the full data analysis. Data are presented as means ± standard deviations for continuous variables and percentages for nominal variables. The primary outcome variable is measured using the chi-square test to evaluate group differences. The secondary outcome variables are measured longitudinally to assess changes over time. Symptoms of anxiety and depression (HADS) will be analysed in continuous-form variables before being transformed to a cut-off score ≥8 for anxiety and depression respectively. We will apply a multilevel logistic model with the time nested within the patient, and Hosmer’s step-down procedure [28] to establish a final model. Analyses will be conducted in R version 3.3.2 (2016-05-03, R Core Team, 2016) (https://www.r-project.org/). Mixed model analyses will be applied for repeated measurement of anxiety (yes/no) or depression (yes/no) using HADS and EQ-5D [29]. Analysis of covariance (ANCOVA) is used to test mean changes between groups, controlling for possible differences at baseline [30, 31]. A paired sampled *t* test is used to analyse mean changes within groups. A statistic will be considered significant when the corresponding *P* value is <0.05. The Statistical Package for Social Sciences (SPSS), version 21 (released 2012, IBM Corp., Armonk, NY, USA) is used for statistical analysis.

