### Secondary outcomes

Anxiety and depression symptoms are measured using the Hospital Anxiety and Depression Scale (HADS) [25, 26], a standardised, self-report instrument consisting of 14 items in two subscales. The 14 items include seven items for anxiety (HADS-A) assessment and seven for depression (HADS-D). Patients rate themselves on each item from 0 (not present) to 3 (maximum), yielding a total possible score of 21 for each subscale. The psychometric properties of the HADS are well documented in research conducted in many different countries; this includes valid use in heart patients [26].

HRQOL and QALY are assessed using the internationally recognised EQ-5D instrument [27]. EQ-5D is a standardised instrument comprising five dimensions of self-reported health status for clinical and economic appraisal. These dimensions are mobility, self-care, usual activities, pain/discomfort and anxiety/depression. The respondent rates himself on each dimension for the degree (no problem, some problem, extreme problem) that best describes his/her present health status.

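### The only repeated-measures HADS model is a logistic model on the ≥8 cut-off, finished by a step-down search that is not said to keep arm and arm-by-time in the model

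*Protocol article*

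**What the plan says.** The Secondary objectives section asks whether the phone support reduces anxiety and depression relative to control over the first year. Under Secondary outcomes, each HADS subscale sums seven items, "yielding a total possible score of 21 for each subscale".

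The section Data management and statistical analysis then lists several analyses:

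- HADS "will be analysed in continuous-form variables before being transformed to a cut-off score ≥8 for anxiety and depression respectively".
- The longitudinal model is logistic and multilevel, with repeated measurements grouped by patient, and it relies on a "step-down procedure [28] to establish a final model".
- "Mixed model analyses will be applied for repeated measurement of anxiety (yes/no) or depression (yes/no) using HADS and EQ-5D".
- ANCOVA on mean changes between groups, adjusted for baseline.
- A paired t "test is used to analyse mean changes within groups".

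The significance threshold is 0.05 throughout. The candidate terms for the step-down, the retention rule and any terms forced into the model are not given.

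**The concern.** Step-down elimination is a tool for building prediction models. A randomised comparison needs a model whose treatment terms are fixed before the data are seen. If arm or arm-by-time must survive a p-value filter, a dropped effect yields no estimate. A retained effect is reported with a p-value and confidence interval that treat the final model as if it had been chosen in advance.

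The model that uses all the visits is also the one that reduces a 0–21 score to yes/no. The continuous score is planned for, but no repeated-measures model is attached to it.

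The paired t tests compare before with after inside one arm. Both arms have valve surgery, so either may change for reasons unrelated to the phone support. A significant change in one arm and not in the other is not a test of the difference between them.

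At stake is the credibility and precision of the secondary conclusion on anxiety and depression.

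**Working it through.** **The plan's own figure.** The article gives no power or precision figure for HADS. Its one calculation, under Sample size and power calculation, is for readmission: 15% against 5%, chi-square test, 5% level, at least 80% power, 286 patients. Two-sided without continuity correction, this gives 141 per arm (282 in total), and 143 per arm gives 80.8% power. The figure reproduces, but it does not bear on HADS. Only the 143 per arm is carried forward.

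**Information lost by the cut-off.** For a normal score cut so that a share p lies at or above the cut, the efficiency relative to the continuous score is φ(z)² / [p(1−p)], where z is the (1−p) normal quantile. The nearest prevalence in the article is in the Background: about 29–61% with moderate to severe anxiety and depression in the first month after cardiac surgery. It is not stated to be HADS ≥8, so using it here is an assumption. The last two rows lie below that range and are assumptions for sensitivity.

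| p | φ(z) | p(1−p) | Efficiency | Loss | Equivalent of 286 patients |
|---|---|---|---|---|---|
| 29% | 0.3423 | 0.2059 | 0.569 | 43% | 163 |
| 50% | 0.3989 | 0.2500 | 0.637 | 36% | 182 |
| 61% | 0.3837 | 0.2379 | 0.619 | 38% | 177 |
| 20% | 0.2800 | 0.1600 | 0.490 | 51% | 140 |
| 15% | 0.2332 | 0.1275 | 0.426 | 57% | 122 |

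**The same loss as power.** This takes one visit, complete data and 143 per arm. The shift detectable with 80% power on the continuous score is (1.960 + 0.842) × √(2/143) = 0.331 SD. Applying that shift and testing the proportions at or above the cut gives:

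- Control 29%, intervention 18.8%: power 52%.
- Control 50%, intervention 37.0%: power 60%.
- Control 61%, intervention 47.9%: power 60%.
- Below the article's range (assumption): 45% at a control prevalence of 20%, and 39% at 15%.

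**Effect of the step-down.** Null logistic data were simulated 2,000 times with 286 patients, one time point, eight candidate covariates and backward elimination at p > 0.05. The covariates and their effects are assumptions.

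| Model | Null runs with a significant or retained treatment term |
|---|---|
| Fixed in advance | 5.3% |
| Step-down on covariates, treatment forced in | 5.35% |
| Step-down, single treatment term also removable | 5.35% |
| Step-down with four treatment-by-covariate interactions also candidates | 24% |

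The simulation error at 5% is about √(0.05 × 0.95 / 2000) = 0.5 percentage points, so the first three rows are indistinguishable. Searching over covariates does no harm to the error rate. Nor does exposing a single treatment term, although its estimate then appears only when it is significant. The excess comes when several treatment terms compete for retention. The 24% illustrates that mechanism. It is not an estimate for this trial, whose candidate terms are not stated.

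**The case against.** The strongest reply is that the article does keep the full score in a randomised comparison. It plans HADS in continuous form, and the baseline-adjusted ANCOVA tests mean changes between the arms. A reader might infer from the logistic model that the yes/no score carries the whole HADS comparison. The text does not support that. The loss from dichotomising applies to the cut-off model and not to every HADS analysis.

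The second reply is that candidate and forced terms are detail that an article leaves to the full protocol or SAP. The article never says that arm may be dropped, and the source cited for the procedure is not at hand. This also stands in part: inflation of the error rate is conditional and not shown. What it does not answer is that the article commits to a data-driven search for the final form of its only longitudinal HADS model, which is a poor choice for a randomised effect wherever the details are written.

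Third, ranking secondary analyses is ordinary SAP content, and the paired t tests are labelled as within-group. Both are fair. The paired tests should not be counted as a further answer to the between-group question. They simply do not address it.

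**Conclusion.** The point holds in limited form. The longitudinal HADS model is dichotomised, and its final form is left to a step-down search that is not said to protect arm and arm-by-time. If those terms are open to removal, inference on the randomised effect ignores its own selection. If only baseline covariates are searched, the error rate stays near 5%.

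The cut-off costs roughly 36–43% of the information within that model. This assumes an approximately normal score and that the Background's 29–61% applies to HADS ≥8. HADS is bounded and may be skewed, so the figures are approximate.

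Two stronger readings should be resisted:

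- A loss of about half needs a prevalence near 20%, which the article does not give.
- Counting three scales at four visits as twelve tests gives 1 − 0.95¹² = 46% for at least one false positive. The article does not say that ANCOVA is run that way, and results on related scales in the same patients are not independent.

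HADS is a secondary outcome. The readmission comparison, by chi-square test, is unaffected. This is a should-fix.

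**What to change.** For HADS-A, HADS-D and the EQ-5D score, specify one linear mixed model each on the continuous score. The fixed terms are arm, visit (1, 3, 6 and 12 months), arm-by-visit, baseline score and baseline-by-visit, with patient as the cluster and no removal of terms. Name one contrast per scale as the secondary result, for example the arm difference at 1 month, when the phone support ends.

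Report the ≥8 proportions as supportive, from a model with the same fixed terms. Confine step-down to exploratory work on predictors. Show within-group change descriptively, without paired tests.

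The cost is a rewording of the analysis section, with the same data and no extra collection. The one loss is that the ≥8 result becomes supportive where it now stands level with the continuous analysis. The article reports recruitment still open at submission and data entry held back until the intervention is finalised, so on that timetable the change could be made without sight of results.

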### Missing data

The amount of missing data in the study and the methods used to handle missing data in the analysis will be reported [32]. Complete registry data will be available on primary outcome readmission 30 days after discharge for sAVR. If a patient dies within 30 days, it will be counted as readmission. Out of a total sample of 286 sAVR patients, we estimate 0–2 deaths. These numbers will not influence the power of the study. Regarding secondary outcomes, the guidelines in the article of Little et al. [32] will be followed; hence, we will perform multiple imputation analyses in analyses where missing data are not handled properly otherwise. In addition, sensitivity analyses will be performed to assess the robustness of assumptions made.

### Narrative data analysis

#### Data/narratives from patients’ phone calls to hospital and project coordinator phone calls to patients

All qualitative data are transcribed verbatim and analysed in several steps using systematic text condensation in accordance with the approach of Malterud [33]. Experts in qualitative analysis in the research group responsible for the AVRre study will re-read the narratives independently before the subsequent data reduction into meaning units, condensed meaning units, subthemes and themes guided by the study’s aim.

### Mixed methods

Qualitative data as narratives from the patients are intended to complement and enrich the quantitative data from study measures. Using narratives from patients’ phone calls will focus on the spontaneous needs and symptoms from the patients’ perspective, thus avoiding recall bias that may occur during interviews at a later time. The two approaches are planned to be used in tandem to answer the research questions in this study [34]. One challenge that needs to be figured out is how to interpret conflicting results.

### Sample size and power calculation

In 2013, a total of 503 patients had aortic valve replacement surgery at Oslo University Hospital. To estimate the sample size required to make confident conclusions about the primary outcome — the number of readmissions 30 days after discharge from hospital — we used published data on readmissions in Norway for patients >65 years old. Seventeen percent of the patients are readmitted to hospital within 30 days from discharge [6]. A sample size of 286 patients with 143 patients in each group will achieve at least 80% power to detect an expected difference of 15% in the control group and 5% in the intervention group at the 5% significance level using the chi-square test.

### Ethical considerations: ethics and disseminations

The study is conducted in accordance with the Declaration of Helsinki. Ethical approval was obtained from the Regional Committees for Medical and Health Research Ethics (approval 2013/2031-3). All patients receive both verbal and written information about the aim of the study and are informed that they are free to withdraw from the study at any time. Patients sign an informed consent document prior to inclusion. The codebook with study numbers and person-sensitive information and data from phone calls is kept in a locked, firewall-secured cabinet. To be able to perform the cost-utility analysis, we included in the written, informed consent form the patients’ permission to collect person-identifiable sensitive data from the medical record and from the Patient Registry Department at the Norwegian Directorate of Health. The results are presented so that the identity of the subjects cannot be identified, either directly or from derived information. Results from this study will be published in peer-reviewed journals.

## Discussion

This randomised controlled study, which we call AVRre, is the first programme to offer and test the effectiveness of a complex 24/7, around-the-clock intervention to optimise sAVR patients’ safety and healthcare in the vulnerable readmission phase 30 days after discharge. The intervention is complex, because phone calls are made proactively to the patient 2 and 9 days after discharge, and because telephone support from expert healthcare professionals is made available day, evening and night during the first 30 days after hospital discharge. Combining experimental and explorative approaches results in mixed-method data, which will strengthen the conclusions we can draw and produce more solid information about sAVR patients’ experiences at home.

Analyses of patient narratives about the symptoms they experience and their needs during early rehabilitation will produce new insights for developing effective patient information systems and education programmes relevant for sAVR patients in the future. Moreover, symptom monitoring combined with evidence-based and clinical expertise advice can accommodate patients’ desires to feel secure and to submit their requests for information after discharge from hospital [14]. Moreover, as we have hypothesised, this should reduce the number of 30-day hospital readmissions and reduce symptoms of anxiety and depression. Readmissions after sAVR are sparsely documented in the research literature, and reports of readmissions in RCTs, except for a few registry studies/observational studies, are almost unknown [8].

Mixing both quantitative and qualitative methods in this RCT increases the probability of obtaining valuable empirical knowledge from sAVR patients in addition to evidence of treatment effect [34]. First, triangulation generated by different data sources is possible; e.g. suppose a patient in the intervention group has a high score for anxiety on HADS, and that patient calls the AVR 24/7 phone to elaborate on and get advice for a case he felt anxious about after sAVR. This would validate information that stems from the instrument.

Prevention of missing data to increase the representativeness of the sample in this trial is related to both designing and conducting the trial [32]. In designing the intervention, former patients and interdisciplinary specialists in the cardiac field revealed the themes for the intervention manual and 24/7 follow-up after discharge, in accordance with evidence-based literature. Moreover, the intervention is flexible, as it is based on when the patients need support. The patients in the control group receive information at discharge about group allocation and the importance of comparing the intervention and the control group in order to offer future sAVR patients a solid follow-up based on patients’ needs. When conducting the study, the participants’ burden and inconvenience of data collection is limited to only two questionnaires with a few items, to avoid missing values and drop-out. The project coordinator is dedicated to follow up the participants and the expert nurses responsible for the 24/7 intervention to limit missing data in the conduct of the study. It is time-consuming to carry out a 24/7 phone support service, and it requires expert healthcare professionals to be deeply and continuously motivated to seriously carry out the study. This is an ongoing challenge, and it is necessary to safeguard the strength of the study. The intervention is bolstered by experiencing and discussing patient cases and by the teaching of relevant themes during the intervention period. Moreover, assessment of the intervention’s cost utility will provide valuable information for the healthcare system to develop ways to improve the transition of patient care to reduce readmissions [35]. Furthermore, knowledge from this study may add valuable information to optimize healthcare for future comparison to the emerging transcatheter aortic valve implantation (TAVI) patient population.

Insight into an individual patient’s pathway through the readmission process is made possible for the first time by patients’ agreeing to allow researchers to gain access to register data. A normal pathway for a patient undergoing sAVR is to be transferred from an index, specialised hospital to a non-index hospital with a lower level of care at the fourth day after surgery. Fragmented care, which can occur when patients are transferred between hospitals at different levels in healthcare systems, increases the risk of mortality [5] and is a present challenge for patients and the healthcare system. This study is limited in that it includes patients only at one university hospital with two departments.

Before surgery, the patients are informed about the expected increase in health status after surgery. Adding the QALY analysis takes into account both the quantity and quality of life generated by healthcare intervention and may add valuable preoperative information for future patients undergoing sAVR.

The lack of masking in this study related to patients may have a potential influence on outcomes [24]. Patients are informed about group allocation 1–2 days before discharge from the University Hospital. If a patient from the control group and one from the intervention group by coincidence are in the same room, the project nurse has organised separate information about further follow-up in the study. The patient in the intervention group is encouraged not to share information about the intervention. The general information of the ongoing AVRre study at the Department might influence the patient in the control group and the caregivers, e.g. to offer more information than usual care and possibly threaten internal validity (the Hawthorne effect).

In conclusion, the knowledge gained from this study will provide valuable insights for adjusting aspects of the healthcare system now to improve care for patients undergoing sAVR and will inform future studies on sAVR. The 24/7 phone-support manual has the potential to be modified and adopted for use by other surgical populations with high readmission rates.

### Trial status at the time of initial manuscript submission

Recruitment for this trial is ongoing.

## Abbreviations

DRG: Diagnosis-related group
EQ-5D: EuroQol-5 dimensions
HADS: Hospital Anxiety and Depression Scale
HRQOL: Health-related quality of life
QALY: Quality-adjusted life year (QALY)
sAVR: Surgical aortic valve replacement
